### Study intervention

2.9.

DTxO is an investigational therapeutic intervention for obese patients, under clinical validation with a randomized and placebo-controlled clinical trial for confirmatory purposes. DTxO is downloadable software for mobile devices (smartphone, tablet), classified as Class IIa Medical Device (MD), available for patients as an application (App) that integrates different non-pharmacological approaches. It is intended to improve weight loss, weight-loss maintenance, and overall health in patients with obesity by increasing their self-engagement, self-monitoring and adherence to dietary/exercise and behavioral programs. The App integrates different non-pharmacological approaches, engaging the patient through monitoring of her/his/them non-vital parameters, monitoring of patient diet and exercise, monitoring of patient psychological status, prescription of exercise and diet in a weight-loss program, and configurable data presentation charts for provision of additional information to professional users.

The Investigational Medical Device (IMD) consists of a Medical Web Application, also called Medical Dashboard, integrated into the electronic Case Report Form (eCRF), where the physician will collect patient's data necessary for enrolment and profile creation; and a Patient App, which will allow interacting with the patient to guide their behaviors, record therapeutic outcomes and improve therapeutic adherence.

The DTxO App will provide a dietary regimen with a personalized advice program, a tailored physical exercise program, a cognitive–behavioural assessment and support program, alerts and reminders, dedicated section on prescribed drugs intake and dietary and exercise program, chat and online visits with clinical professionals, and trophies to improve patient engagement. All these tools aim not only to weight loss, but they also help patients to improve their health and ameliorate their lifestyle.

The user downloads the App, creates their own account and starts to use it at baseline visit, by answering to psychological questionnaires and inserting food preferences. Thereafter, the app is synchronized with physician platform, so that a dietary regimen and a physical activity program is developed. The user then, helped by alerts and reminders, should daily use the app for consulting and filling in dietary, physical activity, and cognitive-behavioural sections, follow thee app's advice, be encouraged and self-monitor the situation. The App sends feedback and changes its advices, customizing them on the patient and going hand in hand with the constant use by the patient. The experimental arm will be compared with a control arm in which dietary and exercise programs will be delivered through a standard paper-based approach. The control arm will also be equipped with a placebo App, not customized on the habits and feedback of the patient, with no alerts and reminders nor chat or online visits.

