It is in this context that digital health tries to respond to the patient's needs and makes the management of this condition more accessible (15). Scientific research has investigated different options of weight loss programs (computer, TV programs, smartphone applications), in order to meet patient's necessities and make obesity treatment more available (15). Smartphones indeed can be a valid option becoming a self-education device holding the capacity to reduce healthcare's workload and treat more people through the partial replacement of traditional medical consultation with digital or telephone management (16, 17). This approach seems the most convenient and accessible, considering the widespread use of smartphones among the population and the fact that weight-loss apps (Apps) can help reinforce dietary plan compliance, physical activity, and weight monitoring with the expedient of progress awareness through goals' achievement (18, 19). Consistent with these findings, our study aims to assess the safety and performance of a Digital Therapy for Obesity App (DTxO) for weight loss and its maintenance in patients affected with obesity undergoing an experimental non-pharmacological treatment. The primary objective is to evaluate the weight loss in patients using DTXO compared to control patients (Placebo App patients DTXO after a period of 6 and 12 months of DTXO use. The secondary objectives are:
1.To assess the degree of dietary recommendation adherence (Mediterranean dietary pattern questionnaire) and of improvement of food and nutrition knowledge (Food Knowledge Moynihan Questionnaire) of the two groups during our study2.To evaluate the reduction of physical inactivity (reduction) (IPAQ Questionnaire), lower limbs physical function improvements (SPPB test) randomized in the two randomized group.3.To measure the reduction of stress (DASS-21 scale), the increase in goodwill to approach therapy (URICA-28 scale), the increase in the (various) self-esteem in coping with life's challenges (GSES-10), the measure of Binge Eating Behaviour (BES-16 scale), the measure of emotion regulation problem (DERS-36 scale), the increase of quality of life (PGWBI questionnaire), the measure of sleep habits (PSQI) in each randomized group4.To identify the level of acceptability in the use of DTxO after 12 months

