#### Exclusion criteria

2.4.2.

•Diseases: recent cardiovascular event (<6 months), heart failure (class >II), GFR <60 ml/min, type 1 diabetes, cancer within the first 5 years; drug or alcohol abuse, active eating disorder or history of bulimia and anorexia nervosa, Binge Eating Scale score >27, psychiatric disorders not compensated, score ≥2 in the “Depression,” “Anxiety” and “Psychoticism” subscales of the Symptom Checklist-90-R; visual or vision impairments; secondary obesity, Edmonton Obesity Staging System score >4; bariatric surgery in the previous 2 years; referred pain to lower limb joints on the Numeric Rating Scale ≥5; recent (<6 months) weight loss ≥10%.•Prior/Concomitant Therapies and other exclusions: Changed in pharmacological therapy with drugs that may affect eating behavior and/or energy metabolism during the last 3–6 months; participation in other weight-loss programs or in other clinical trials; known child-bearing women; any condition could the results of the study. Potentially interfering with the results of the study according to the investigator.

The presence of inclusion criteria and absence of exclusion criteria is investigated during the visit.

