#### Baseline visit (V0)

2.10.1.

During the first visit, the patient will sign the informed consent form and will be evaluated for inclusion/exclusion criteria. Once the enrolment is confirmed, the patient is randomized 1:1 to either the experimental arm (DTx Obesity App) or control arm. The physician will explain to the patient how to download, access, and use the assigned App.

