### Study control

2.11.

The efficacy of the DTXO App will be assessed with the comparison of results with a group of patients treated with a standard of care approach (paper-based, in-person) and a placebo App.

The placebo App will include only the non-medical modules of the digital therapy, for example, patient onboarding data and access, while it will not include any medical module; for example, the digital placebo App will not allow the input of the patient's reported clinical data nor provide indications or reminders about the therapy or diagnosis.

The placebo App has been introduced to make the experience of subjects in the control arm more similar to that of subjects in the experimental arm; moreover, data collection through the placebo app (questionnaires) will streamline the data collection process, avoiding manual data entry and reducing the possibility of entry errors. Through the placebo App, the patient will be asked to complete weekly the Diet Adherence questionnaire (NRS scale). No trend graph will be provided to the patient to monitor their performance, nor any personalized content will be displayed. standard clinical practice. The placebo App will be used only as a data entry tool for questionnaires.

Patients in the control group will be provided with a dietary plan and nutritional education and behavioral contents in paper format.

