## Results

3.

The advantage of the study is the possibility to provide simultaneous treatment strategies to improve the health status of obese patients. We expect that the concurrent application of these strategies and the possibility of customizing patients' activities based on their habits and feedback will allow greater benefits than the application of separate, no customized programs and a standard paper-based in- person approach. Both treatment arms will receive potential benefits by participating in this study.

The control arm will receive the current standard of care (paper-based approach and face-to-face follow-up visits) for obese patients with the addition of a placebo app. However, greater benefits are hypothesized in the experimental arm due to the possibility of customization of physical activity in accordance with the perceptions and feedbacks of the patient, the availability of notifications and reminders for drug intake (dosage, frequency) to improve treatment adherence, the availability of contents to support and favor compliance with the prescribed diet, the possibility to schedule an online visit or communicate with the clinical specialist via chat through the App, and the availability of multimedia psycho-behavioral content (motivational exercises, self-acceptance exercises, mindfulness exercises, interactive emotional eating exercises, self-efficacy exercise).

Differences between the DTxO and the App placebo are reported in Table 1.

**Table 1 T1:** Differences between the dTxO and the App placebo.

	DTXO	App placebo
Diet		
Dietary plan and personalized suggestions’ alerts	X	
Dietary questionnaires		
Mediterranean-style eating questionnaire	X	X
Questionnaire food knowledge Moynihan questionnaire	X	X
Dietary program self- assessment		
Diet adherence (NRS scale)	X	X
Diet enjoyment (NRS scale)	X	
Hunger/satiety scale (NRS scale)	X	
Physical activity		
Physical activity plan	X	
Physical activity program self- assessment		
Level of physical activity questionnaire (IPAQ)	X	X
Fatigue perceived (NRS scale), Pain perceived (NRS scale)	X	X
Psycho-behavioural assignment		
Psychobehavioural self- assessment	X	X
DASS-21, URICA-28, GSES-10, BES-16, DERS-36, PGWBI, PSQI		
Recording of concomitant medications	X	
Telemedicine/remote contact	X	

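### As described, the baseline-visit psychological questionnaires are answered after randomisation inside the assigned app, so the first scores for these secondary endpoints are not pre-randomisation values

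*Protocol article*

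**What the plan says.** All references are to the protocol article.

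- **2.10.1 Baseline visit (V0).** Consent and the eligibility check come first. Then: "Once the enrolment is confirmed, the patient is randomized 1:1 to either the experimental arm (DTx Obesity App) or control arm". The next sentence reads: "The physician will explain to the patient how to download, access, and use the assigned App".
- **2.9 Study intervention.** The user downloads the app, opens an account and "starts to use it at baseline visit, by answering to psychological questionnaires and inserting food preferences". The programme comes afterwards: "Thereafter, the app is synchronized with physician platform, so that a dietary regimen and a physical activity program is developed".
- **2.11 Study control.** For the control arm: "The placebo App will be used only as a data entry tool for questionnaires".
- **Table 1 (section 3, Results).** Psychobehavioural self-assessment is marked for both apps, with the scales "DASS-21, URICA-28, GSES-10, BES-16, DERS-36, PGWBI, PSQI".
- **Section 1, secondary objectives.** Several of these scales are objectives worded as change, for example "To measure the reduction of stress (DASS-21 scale), the increase in goodwill to approach therapy (URICA-28 scale".
- **2.4.2 Exclusion criteria.** One of the same instruments also decides eligibility: "Binge Eating Scale score >27".

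**The concern.** Randomisation makes the arms comparable on anything measured before allocation can influence it. A baseline score taken after allocation, in the app the patient has been assigned, loses that guarantee. Motivation to change, self-efficacy, stress and wellbeing are self-reported and plausibly sensitive to what the patient expects of the treatment.

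The two apps differ in content. Under 2.9 and 2.11 the placebo app has no reminders, chat, online visits or personalised material, and control patients receive their programme on paper. If a patient answers more hopefully, or less so, because of the app just explained, the starting point moves in one arm and the comparison of change moves with it. The error can run either way. For example, an encouraged active arm starts from a better score and then shows less improvement.

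What is at stake is the interpretation of seven secondary scales, in a trial that 2.9 presents as confirmatory.

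**Working it through.** **1. The plan's own figure, to see whether it is touched.** Inputs from 2.12.1: difference 1.5 kg, SD 3.5 kg, two-sided alpha 0.05, power 80%, 1:1 allocation, drop-out 30%.

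- n per arm = 2 × (1.96 + 0.8416)² × 3.5² / 1.5² = 2 × 7.849 × 5.444 = 85.5, rounded up to 86, so 172 in total. Power at 86 per arm is 0.802.
- Allowing for drop-out: 172 / 0.70 = 245.7, rounded up to 246.

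Both stated figures reproduce. They rest on weight, not on a questionnaire, so this point leaves them unchanged.

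**2. Order of events at V0.**

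| Step | Event | Source |
|---|---|---|
| 1 | Consent, eligibility check | 2.10.1 |
| 2 | Randomisation | 2.10.1 |
| 3 | Physician explains the assigned app | 2.10.1 |
| 4 | App downloaded, account opened, psychological questionnaires answered | 2.9 |
| 5 | App synchronised, diet and activity programme developed | 2.9 |

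Step 4 follows step 2 because the app in use is the assigned one. The sentence in 2.9 is written in the description of DTxO. For the control arm, the same order follows from 2.10.1 (the assigned app is handed over after randomisation), 2.11 (the placebo app is where questionnaires are entered) and Table 1 (the same self-assessment in both apps). The article describes no earlier administration of these scales, apart from the BES score that eligibility implies. The answers are therefore post-randomisation (after step 2) but precede the personalised programme (before step 5).

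**3. How a shift would carry through.** Let seeing the assigned app move the baseline answers by s SD more in one arm than in the other, with follow-up scores unaffected by that shift. Let r be the correlation between baseline and follow-up, with equal SDs so that the regression slope equals r.

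- Change from baseline: bias has size s.
- Baseline-adjusted comparison: bias has size r × s.
- Comparison of follow-up scores only: no bias from this source.

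The sign is opposite to the shift. The documents give neither s nor r, so the values below are assumptions that show the range.

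| s (SD) | Change score | Adjusted, r = 0.3 | Adjusted, r = 0.5 | Adjusted, r = 0.7 |
|---|---|---|---|---|
| 0.05 | 0.05 | 0.015 | 0.025 | 0.035 |
| 0.10 | 0.10 | 0.03 | 0.05 | 0.07 |
| 0.20 | 0.20 | 0.06 | 0.10 | 0.14 |

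If s is zero, there is no bias under any of these analyses.

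**The case against.** The strongest reply has three parts.

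**Blinding.** Section 2.8 says the placebo app is there to keep patients unaware of their allocation, and both arms answer the same listed instruments. If blinding holds while the account is being set up, there is no differential shift. This lessens the risk but does not remove it: the physician has already explained an app whose functions differ by arm, and a baseline taken before allocation would not depend on the blind at all.

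**No stated analysis baseline.** The sentence in 2.9 describes how app use begins. It is not a schedule of assessments, and nothing in the article expressly calls these answers the analysis baseline. A full protocol or analysis plan, not shown, may define it. This stands as a limit on the point: that these scores serve as baseline is an inference. The order of events, however, is stated rather than merely left out.

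**BES and eligibility.** A reader might infer that patients with a disqualifying BES score will be discovered only after randomisation. The documents do not support that. Section 2.4.2 has the criteria checked at the visit, 2.10.1 randomises only after enrolment is confirmed, and 2.9 describes a Medical Dashboard within the eCRF for the data that enrolment needs. A route to a pre-randomisation BES score therefore exists. What stays open is whether that score or the in-app one is the baseline.

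**Conclusion.** The point holds as a minor one. As written, the first described scores on the seven psychological scales are obtained after randomisation, in arm-specific software and after that software has been explained. Any resulting bias equals the differential shift for change scores and r times the shift for baseline-adjusted analyses. The documents do not show that a shift occurs or how large it would be. The conclusion assumes that these in-app answers serve as the baseline.

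Four stronger readings are tempting and should not be drawn:

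- **That the scores are not pre-treatment values.** Section 2.9 develops the programme only after the questionnaires, so they precede the personalised treatment.
- **That patients have already seen what the app offers.** The article says only that its use is explained to them.
- **That all patient-reported endpoints are affected.** The timing of the baseline IPAQ, Mediterranean diet and food-knowledge questionnaires is not stated.
- **That the bias is a given share of the detectable effect.** The only effect size in the plan, 1.5 / 3.5 = 0.43 SD, belongs to weight. The questionnaires have no stated target difference, so dividing an assumed shift by it tells us little.

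**What to change.** In 2.9 and 2.10.1:

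- State that the seven psychological questionnaires are completed and locked after consent and before allocation is released. Use either the eCRF/Medical Dashboard, which 2.9 already provides, or an onboarding module identical in both arms.
- Name those locked values as the baseline for the secondary analyses.
- State that the BES score used for the exclusion criterion is this same pre-randomisation score.
- Release the allocation and install the assigned app only after that.

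The cost is one reordered visit, a questionnaire module opened earlier, and a slightly longer V0 before randomisation. The sample size and the primary analysis do not change.

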### Measurements and procedures

2.10.

#### Baseline visit (V0)

2.10.1.

During the first visit, the patient will sign the informed consent form and will be evaluated for inclusion/exclusion criteria. Once the enrolment is confirmed, the patient is randomized 1:1 to either the experimental arm (DTx Obesity App) or control arm. The physician will explain to the patient how to download, access, and use the assigned App.

#### Follow-up visit

2.10.2.

After the baseline visit, the patient will follow the dietary, physical and psycho- behavioural programs suggested by the physician and will use the DTXO/placebo App as explained by the physician. Face-to-face follow-up visits are foreseen at 3 months (V1), 6 months (V2), 9 months (V3) and 12 months (V4) after enrolment. During each visit, the following assessments are performed:
•Physical examination•Assessment of vital signs•Laboratory blood tests•Short Physical Performance Battery•Assessment of patient's responses to psycho-behavioural questionnaires by a psychologist. If any psycho-pathological problem is detected, the patient is referred to a specialist and exits the study.•Recording of concomitant medications•Safety assessment (adverse events investigation)

#### Telemedicine/remote contact

2.10.3.

The Telemedicine visit and the remote contact between the patient and the physician will occur in specific situations related to weight- loss changes. This remote contact will allow the physician to understand the entity of the patient's symptoms and to manage them promptly. These utilities are part of the digital therapy: together with DTXO App, they will help patients to achieve treatment goals and assist them. To guarantee a proper assistance to all patients, control group was provided with email address and telephone number of enrolment outpatient clinic in case of need.

### Study control

2.11.

The efficacy of the DTXO App will be assessed with the comparison of results with a group of patients treated with a standard of care approach (paper-based, in-person) and a placebo App.

The placebo App will include only the non-medical modules of the digital therapy, for example, patient onboarding data and access, while it will not include any medical module; for example, the digital placebo App will not allow the input of the patient's reported clinical data nor provide indications or reminders about the therapy or diagnosis.

The placebo App has been introduced to make the experience of subjects in the control arm more similar to that of subjects in the experimental arm; moreover, data collection through the placebo app (questionnaires) will streamline the data collection process, avoiding manual data entry and reducing the possibility of entry errors. Through the placebo App, the patient will be asked to complete weekly the Diet Adherence questionnaire (NRS scale). No trend graph will be provided to the patient to monitor their performance, nor any personalized content will be displayed. standard clinical practice. The placebo App will be used only as a data entry tool for questionnaires.

Patients in the control group will be provided with a dietary plan and nutritional education and behavioral contents in paper format.

### Statistical analysis

2.12.

#### Calculation of sample numerosity

2.12.1.

Considering the primary endpoint, an 80% power and a two-sided type I error of 0.05 would be reached with a global sample size of 172 patients (86 per group) in order to be able to measure a 1.5 kg weight change after 6 months between the two groups, assuming an SD of 3.5 kg and a drop-out rate of 30%. We hence established a target of 246 patients considering a drop-out rate of 30%.

#### Data analysis

2.12.2.

We will perform descriptive analyses (at each visit) by computing categorical variables (percentages and frequencies) and continuous variables (mean and median values, standard deviations, quartiles, and extreme values). If useful, descriptive data will also be examined graphically through histograms and box-and-whisker plots. Appropriate statistical methods for comparisons between- group (i.e., interventional vs. control group) and within-group will be applied according to the nature of the variables (continuous or categorical variables), as specified in the following sections. % CI will not be finalized before the. Data analyses will be conducted using SAS version 9.4 (SAS Institute, Cary, NC, USA) statistical software.

## Results

3.

The advantage of the study is the possibility to provide simultaneous treatment strategies to improve the health status of obese patients. We expect that the concurrent application of these strategies and the possibility of customizing patients' activities based on their habits and feedback will allow greater benefits than the application of separate, no customized programs and a standard paper-based in- person approach. Both treatment arms will receive potential benefits by participating in this study.

The control arm will receive the current standard of care (paper-based approach and face-to-face follow-up visits) for obese patients with the addition of a placebo app. However, greater benefits are hypothesized in the experimental arm due to the possibility of customization of physical activity in accordance with the perceptions and feedbacks of the patient, the availability of notifications and reminders for drug intake (dosage, frequency) to improve treatment adherence, the availability of contents to support and favor compliance with the prescribed diet, the possibility to schedule an online visit or communicate with the clinical specialist via chat through the App, and the availability of multimedia psycho-behavioral content (motivational exercises, self-acceptance exercises, mindfulness exercises, interactive emotional eating exercises, self-efficacy exercise).

Differences between the DTxO and the App placebo are reported in Table 1.

**Table 1 T1:** Differences between the dTxO and the App placebo.

	DTXO	App placebo
Diet		
Dietary plan and personalized suggestions’ alerts	X	
Dietary questionnaires		
Mediterranean-style eating questionnaire	X	X
Questionnaire food knowledge Moynihan questionnaire	X	X
Dietary program self- assessment		
Diet adherence (NRS scale)	X	X
Diet enjoyment (NRS scale)	X	
Hunger/satiety scale (NRS scale)	X	
Physical activity		
Physical activity plan	X	
Physical activity program self- assessment		
Level of physical activity questionnaire (IPAQ)	X	X
Fatigue perceived (NRS scale), Pain perceived (NRS scale)	X	X
Psycho-behavioural assignment		
Psychobehavioural self- assessment	X	X
DASS-21, URICA-28, GSES-10, BES-16, DERS-36, PGWBI, PSQI		
Recording of concomitant medications	X	
Telemedicine/remote contact	X	

